##### Attendance rate

The attendance rate of Tai Chi training will be monitored by instructors. Sign-in sheets will be used to monitor attendance.

##### Data collection

The reviewer will record data using the Research Electronic Data Capture (REDCap), which is a password-protected system. All data will be double-checked by a second reviewer. Participants will be contacted about the study outcomes in the case of missing data.

### Statistical analysis

The statisticians and researchers will establish a statistical plan. It will contain baseline characteristics, treatment effects, adverse events, and attendance evaluations. All analyses will be conducted using the intention-to-treat method. Two independent sample t-tests will be used for analysis. Repeated measures analysis of variance will be used to examine the effects of VAS between the Tai Chi group and the control group. We will use the Wilcoxon-Signed Rank Test to assess non-normally distributed data. Continuous data will be expressed as mean ± standard deviation. The chi-square test will be used for categorical data. We will set the statistical significance at a *P*-value of < 0.05. Missing data will be processed according to the last observation carry-forward rules. We will use IBM SPSS Statistics version 25 (SPSS, Inc., USA) for data analysis.

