**Methods:**

The study design will be a randomized, controlled, open-label trial. Participants (*n* = 106) will be recruited from the Hospital of Chengdu University of Traditional Chinese Medicine, Qing Yang District University for the Elderly, and Ci Tang Street Community. Participants will be randomly assigned to the Tai Chi group (*n* = 53) and the control group (*n* = 53). The Tai Chi group will undergo a Yang-style 24-form Tai Chi program for 8 weeks. The control group will have a waiting period of 8 weeks, followed by 8 weeks of Tai Chi practice. The primary outcomes of this study will be changes in sleep quality and pain intensity. Secondary outcomes of interest will include changes in the quality of pain, range of motion, physical performance, social support, and overall quality of life. Any adverse events and attendance rates will also be reported in this study.

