## Methods

### Study design

This study design conducts an open-label, randomized, controlled trial. The study protocol was approved by the Ethics Committee of the Hospital of Chengdu University of Traditional Chinese Medicine in Sichuan Province on 06/06/2022 (ethics approval number: 2022KL-038-02). This trial is registered with the Chinese Trial Registry under the number ChiCTR2200064977. This protocol adheres to the Consolidated Standard of Reporting Trials (CONSORT) and the Standard Protocol Items: Recommendations for Interventional Trials (SPIRIT). This study will be conducted at the Hospital of Chengdu University of Traditional Chinese Medicine, Qing Yang District University for the elderly, and Ci Tang Street Community. We will compare the effects of the Tai Chi group against the control group on insomnia in elderly people with CNLBP. Baseline assessments and follow-up assessments will be conducted at weeks 8, 16, 32, and 40 to measure primary outcomes such as sleep and pain intensity as well as secondary outcomes such as quality of pain, range of motion, physical performance, social support, quality of life, attendance rate, and adverse events. The detailed schedule of patient interventions and outcomes is described in Table 1.

**Table 1 T1:** Schedule of patients, intervention, outcomes.

**Item**	**Week 0**	**Week 1–8**	**Week 8**	**Week 9–16**	**Week 16**	**Week 32**	**Week 40**

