### Procedures

#### Randomization and blinding

Eligible participants will be randomly assigned to two groups in a 1:1 ratio. Randomization will be performed by an independent researcher and will be generated in blocks of varying sizes and stratified according to the central computer system. The group assignments will be hidden in opaque envelopes by an independent researcher who will not participate in the study. The envelopes will be opened for each participant after the completion of the assessments. The instructors and participants will not be blinded to the group assignments. Research assessors and statisticians will be blinded to group allocation.

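### The named group comparisons (t-test; repeated measures ANOVA for VAS) do not adjust for baseline or strata, which costs precision that is free to recover

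*Protocol article*

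**What the plan says.** The Statistical analysis section names the group comparison in one sentence: "Two independent sample t-tests will be used for analysis". For pain it adds: "Repeated measures analysis of variance will be used to examine the effects of VAS between the Tai Chi group and the control group". Other tests are listed for non-normal and categorical data. For PSQI, the t-test is therefore the only normal-theory comparison named. No sentence in the section brings in a baseline value or a stratum.

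The section does not say whether the t-test is applied to follow-up scores or to changes. The Methods part of the abstract points to changes: "The primary outcomes of this study will be changes in sleep quality and pain intensity". The Sample size section also bases its calculation on change in both scores.

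Baseline data will exist. The Study design section says "Baseline assessments and follow-up assessments will be conducted at weeks 8, 16, 32, and 40 to measure primary outcomes", and Table 1 marks PSQI and VAS at week 0.

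Under Randomization and blinding, the allocation sequence is "generated in blocks of varying sizes and stratified according to the central computer system". No stratification factor is given.

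The Statistical analysis section also announces a separate document: "The statisticians and researchers will establish a statistical plan". That plan is not available.

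**The concern.** When an outcome is measured before randomisation and again afterwards, the baseline value is usually its best single predictor. A t-test on follow-up scores ignores it. A t-test on changes subtracts all of it, which over-corrects whenever the correlation is below 1. ANCOVA estimates how much to subtract and is at least as precise as either. The eligibility criteria set no PSQI or VAS threshold, so good and poor sleepers can both enter, and baseline scores may spread widely.

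Two things are at stake. One is precision, in a trial planned on only 96 evaluable participants. The other is that a chance baseline difference between the arms passes into the observed treatment difference, in a direction that depends on which t-test is used. Because the article leaves the choice between follow-up and change scores open, that choice could also be made after the data are seen.

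If the strata are prognostic, leaving them out of the analysis makes the standard error larger than it need be. They cannot be put in until the article says what they are.

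**Working it through.** **Inputs from the article.** Sample size section: differences of 5 points (PSQI) and 1.96 points (VAS), alpha 0.05, 90% power, 96 evaluable, so 48 per arm at 1:1. No SD and no baseline-to-follow-up correlation are given.

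**The article's own figure.** Without an SD, 96 cannot be reproduced forwards. Working back (two-sided alpha, normal approximation), the standardised difference is

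d = (1.960 + 1.282) × √(2/48) = 0.66,

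which implies an SD of 5/0.6617 = 7.56 for PSQI and 1.96/0.6617 = 2.96 for VAS. These serve only to fix the starting point at 90% power.

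**Assumptions.** Correlation r = 0.3, 0.5 or 0.7; equal variance σ² at baseline and follow-up.

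**Variance ratios.**
- Follow-up score: variance σ². ANCOVA residual variance: (1 − r²)σ². Ratio: 1 − r².
- Change score: variance 2(1 − r)σ². Ratio: (1 − r²) / [2(1 − r)] = (1 + r)/2.

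**Power at 48 per arm.** Power = Φ(3.2415/√ratio − 1.960), where 3.2415 = 1.960 + 1.2816 gives 90% when the ratio is 1. Example, change scores at r = 0.3: 3.2415/√0.65 = 4.021; Φ(2.061) = 98.0%.

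| | r = 0.3 | r = 0.5 | r = 0.7 |
|---|---|---|---|
| ANCOVA / follow-up t-test variance | 91% | 75% | 51% |
| Power, from 90% | 92.5% | 96.3% | 99.5% |
| Total N for 90% power, from 96 | 88 | 72 | 50 |
| ANCOVA / change t-test variance | 65% | 75% | 85% |
| Power, from 90% | 98.0% | 96.3% | 94.0% |
| Total N for 90% power, from 96 | 64 | 72 | 82 |

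The two readings move in opposite directions: the gain over follow-up scores grows with r, and the gain over change scores shrinks with r.

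**Chance imbalance.** The baseline difference between arms has standard error √(2/48) = 0.20 SD, so its 95% range is about ±0.40 SD. At the edge of that range:
- a follow-up t-test carries r × 0.40 = 0.12, 0.20 or 0.28 SD into the estimate;
- a change-score t-test carries (1 − r) × 0.40 = 0.28, 0.20 or 0.12 SD the other way.

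These are in units of the baseline SD. If the planned 0.66 is in follow-up SDs, the first set is 18%, 30% or 42% of the planned effect. If it is in change-score SDs, each equal to √[2(1 − r)] baseline SDs, the second set is 0.28/0.78 = 36%, 0.20/0.66 = 30% or 0.12/0.51 = 23%.

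**Strata.** No factor is named, so the cost of ignoring the strata cannot be calculated.

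**The case against.** The strongest reply has five parts.

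- **VAS is not left to a t-test alone.** Repeated measures ANOVA is named for it and can include week 0 as a time point. This stands, and a claim that both primary outcomes rest only on a t-test would be wrong. But a week-0 time point is not a baseline covariate: with two time points, the group-by-time test is the change-score t-test. No stratum term is named there either.
- **The article points to changes, which already use baseline.** This stands. The change-score figures are the ones to weigh, and they show the smaller gain when the correlation is high.
- **The unadjusted test is valid.** This stands. A reader might infer that the treatment effect would be biased or type I error inflated. The t-test is unbiased over randomisation. The error described above exists only conditional on an imbalance that has occurred, and ignoring prognostic strata generally makes the test conservative.
- **The strata argument is thin.** A reader might infer that the three recruitment settings are the strata and that they differ in pain and sleep. The article says neither, so site is only a candidate.
- **Covariates belong in the statistical plan that is still to be written.** This stands in part. Silence on covariates would be no finding. But the article names its tests affirmatively, and those named are unadjusted. A later plan that adjusts would have to depart from the published method.

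**Conclusion.** The point holds as a loss of efficiency, and most clearly for PSQI. Baseline values that will be collected anyway are not used as covariates. Over assumed correlations of 0.3 to 0.7 with equal variances, adjustment would cut the variance by 15% to 35% against a change-score t-test and by 9% to 49% against a follow-up-score t-test. It would also remove chance imbalance in the baseline score from the estimate.

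A reader might conclude that the trial is underpowered. The calculation does not show that: it takes the stated 90% as given and finds that more is available at the same size. The power gains depend on that starting point and on an SD that the article does not state. If the true SD is smaller than the implied one, power is already above 90% and the gain in power is smaller. The variance ratios do not depend on the SD.

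The sentence on stratification is defective in itself, because a computer system is not a stratification factor. What ignoring the strata costs is unknown.

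This should be changed, but the trial's validity does not depend on it.

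**What to change.** In the Statistical analysis section, replace the t-test sentence, and the repeated measures sentence for VAS, with wording such as: PSQI and VAS at week 8 will be compared between groups by ANCOVA (or a mixed model for repeated measures) with group, the baseline value of the outcome and the factor(s) used to stratify randomisation as covariates; the adjusted mean difference will be reported with its 95% confidence interval. Week 8 is the natural time point, because the control group starts Tai Chi after it.

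Under Randomization and blinding, replace the reference to the computer system with the factor(s) actually used, taken from the randomisation record. Study site should be written in only if the record shows that it was used. If no factor was used, drop the word stratified and the stratum term.

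The cost is a wording change in the protocol and statistical plan plus one check of the randomisation record. It needs no new data, visits or participants. It should be fixed before unblinding, which also closes the open choice between follow-up and change scores.

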### Interventions

#### Tai Chi group

Participants in the Tai Chi group will attend a Yang-style 24-form Tai Chi training program. Each Tai Chi session will last 60 min (10 min warm-up, a 40 min Tai Chi training program, and a 10 min cooldown) three times a week for 8 weeks. The training sessions will be conducted by three experienced instructors.

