#### Control group

The participants in the control group will not receive any interventions for 8 weeks. After 8 weeks, participants will be instructed to do Tai Chi exercises for 8 weeks for 60 min (10 min warm-up, a 40 min Tai Chi training program, and a 10 min cooldown) three times a week. Tai Chi group coaches will also instruct participants.

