## Discussion

This study will compare the effectiveness of Tai Chi in improving insomnia symptoms in elderly people with CNLBP in the Tai Chi group with that in the control group. Previous research showed that Tai Chi provides various benefits for older adults with CLBP, including improvements in functional abilities (such as balance, leg strength, and flexibility), psycho-spiritual support, and social support (Lee et al., 2020). That study was conducted with 18 participants, who were randomized into the Tai Chi group. In our study, 122 participants will be recruited. Previous studies suggest that Tai Chi has protective effects on neuromuscular function in aging individuals with non-specific low back pain, but no follow-up was reported (Zou et al., 2019; Liu et al., 2020). Our study will fill this gap by conducting a 24-week follow-up to evaluate the effects of Tai Chi on insomnia in people with CNLBP. Previous studies mostly focused on the functional benefits of Tai Chi (Wen et al., 2022; Yan et al., 2022). However, this study will aim to test the effectiveness of Tai Chi in treating insomnia in patients with CNLBP.

This trial will have several strengths that increase its validity and reliability. First, the randomized controlled trial design of the study allows for a fair comparison of the effects of Tai Chi on insomnia in patients with CNLBP. Second, the study takes into account multiple factors that affect sleep quality, such as physical, psychological, and social factors. Additionally, the protocol adheres to CONSORT and SPIRIT guidelines.

However, this study will also face some limitations. First, the high expectations of the participants in the Tai Chi group may influence the results. Second, there is a risk of high dropout rates during the waiting period. Finally, the research process may be affected by COVID-19.

The results of this trial may help improve sleep quality and reduce pain in people with CNLBP. Furthermore, they could advocate for the promotion of Tai Chi training as a therapeutic option to treat insomnia in elderly individuals with CNLBP. Tai Chi may be considered a viable therapeutic option for CNLBP patients with insomnia.

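### No primary time point is named for PSQI or VAS, although controls start Tai Chi after week 8, the only post-treatment visit with untreated controls

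*Protocol article*

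**What the plan says.** - **Tai Chi arm** (Protocol article, Tai Chi group): sessions run "three times a week for 8 weeks", so training fills weeks 1-8.
- **Control arm** (Control group): "The participants in the control group will not receive any interventions for 8 weeks". The section continues: "After 8 weeks, participants will be instructed to do Tai Chi exercises for 8 weeks for 60 min". Table 1 accordingly marks the control arm in weeks 9-16.
- **Visits** (Study design): "Baseline assessments and follow-up assessments will be conducted at weeks 8, 16, 32, and 40 to measure primary outcomes". Table 1 also marks VAS in the weeks 1-8 and 9-16 columns, and the Pain intensity section asks for weekly ratings.
- **Primary time point:** none is given in the Abstract, Study design, Sample size, Primary outcomes or Statistical analysis sections. The target differences (5 points on PSQI, 1.96 on VAS) carry no week.
- **Analysis** (Statistical analysis): "Repeated measures analysis of variance will be used to examine the effects of VAS between the Tai Chi group and the control group". Two-sample t-tests are also listed, without a visit. The section adds that a statistical plan will be drawn up.
- **Follow-up claim** (Discussion): "Our study will fill this gap by conducting a 24-week follow-up to evaluate the effects of Tai Chi on insomnia".

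**The concern.** The hypothesis in the Introduction is that Tai Chi does better than the control condition. Only the period up to week 8 tests that against no intervention. From week 9 the controls receive the same programme, and intention-to-treat analysis does not give back an untreated comparator.

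With no primary time point, four post-baseline visits are candidates for the main result, and only one of them has untreated controls. The later visits answer another question, and the arms stand at different distances from training when it is asked. Three things are at stake:

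- The confirmatory comparison is undefined for both primary outcomes.
- A VAS analysis that averages over visits could dilute a real week-8 effect.
- A null difference at week 32 or 40 could be read as absence of lasting benefit when both arms have been treated.

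**Working it through.** **1. What each visit compares.** Training ends at week 8 in the Tai Chi arm and at week 16 in the control arm.

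| Visit | Weeks since training, Tai Chi arm | Weeks since training, control arm | Contrast |
|---|---|---|---|
| 8 | 0 | not yet trained | Tai Chi vs no intervention |
| 16 | 8 | 0 | early vs delayed |
| 32 | 24 | 16 | early vs delayed |
| 40 | 32 | 24 | early vs delayed |

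The weekly VAS ratings in weeks 1-7 also have untreated controls, but they fall before training is complete.

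The 24-week follow-up can be weeks 16 to 40, or week 32 for the Tai Chi arm and week 40 for the control arm. On either reading no arm is untreated.

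**2. The plan's own figure.** The Sample size section gives 96 participants (48 per arm), 90% power and alpha 0.05, but no SD, so 96 cannot be reproduced. Solving backwards with a two-sided t-test, 48 per arm and 90% power gives a standardised effect d = 0.6685. For VAS this implies an SD of 1.96 / 0.6685 = 2.93. I take this d as the week-8 effect.

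**3. Group main effect, if all scheduled VAS times were used.** The assumptions are compound symmetry with correlation ρ = 0.3, 0.5 or 0.7, and an effect profile p (the fraction of the week-8 difference present at each visit). The effective standardised effect is

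d × mean(p) / √[(1 + (K − 1)ρ) / K].

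Five visits (weeks 0, 8, 16, 32, 40), full catch-up by week 16 and benefit held: p = [0, 1, 0, 0, 0], mean 0.2, so the averaged VAS difference is 0.2 × 1.96 = 0.39. For ρ = 0.3: √(2.2/5) = 0.663; 0.2/0.663 = 0.302; 0.302 × 0.6685 = 0.202; power 16%.

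Weekly VAS means weeks 0-16 plus 32 and 40 (19 times), with linear onset over weeks 1-8 and linear catch-up over weeks 9-16: mean 8/19 = 0.421, averaged difference 0.83.

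| Group main effect | ρ = 0.3 | 0.5 | 0.7 |
|---|---|---|---|
| 5 visits, full catch-up | 16% | 13% | 11% |
| 5 visits, half catch-up (mean 0.5) | 69% | 55% | 46% |
| 5 visits, controls never treated (mean 0.8) | 97% | 92% | 85% |
| 19 times, full catch-up | 65% | 47% | 36% |
| 19 times, controls never treated | 99% | 93% | 83% |
| Weekly, weeks 0-8 only (mean 0.5) | 75% | 59% | 47% |

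**4. Group-by-time test on the same data.** Noncentrality = (48/2) × d² × Σ(p − mean p)² / (1 − ρ). With five visits and full catch-up the sum of squares is 0.8. For ρ = 0.3: 24 × 0.447 × 0.8 / 0.7 = 12.3 on 4 and 376 df, power 81%. For ρ = 0.5 and 0.7 power is 93% and 99.5%. With half catch-up it is 58%, 74% and 94%. Five-visit power is the same under full catch-up as with controls never treated, because the two profiles have the same sum of squares. A significant result therefore cannot tell these two situations apart.

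**5. Does narrowing the window cure it?** Not by itself. The last row of the table shows that a main effect over weekly weeks 0-8 reaches only 47-75%, because baseline and the onset weeks are averaged in. The week-8 contrast has 90% by construction.

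**The case against.** The strongest reply is that the Statistical analysis section never says which visits enter the ANOVA or which term is tested. Such details are commonly left to an analysis plan, and the protocol says one will be written. This stands. A reader might infer from Table 1 that the ANOVA runs from week 0 to week 40, but the text does not say so, and dilution cannot be asserted as a property of the plan.

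A reader might also take 11-16% as the trial's power for VAS. That is not supported either. The figure needs the main effect, five visits and full catch-up together. Weekly VAS, which the protocol does schedule, gives 36-65%, and a group-by-time test keeps high power under full catch-up. If Tai Chi has no effect the arms should not diverge, so that test is valid; the objection to it is one of interpretation. Part of the main-effect loss comes from averaging in baseline and onset, not from the crossover.

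Dilution does not extend to PSQI, because the ANOVA is assigned to VAS only. For PSQI the open time point is the whole issue. Finally, the Discussion does not promise an untreated comparator at 24 weeks; it claims follow-up where earlier studies reported none.

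What the reply does not remove is the missing primary time point. It defines the primary outcome and belongs in the protocol, above all in a design where the control condition ends at week 8.

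**Conclusion.** The point holds in a limited form. Established from the text alone: controls are treated from week 9; week 8 is the only post-treatment visit against no intervention; no primary time point is named for PSQI or VAS; the t-tests and the VAS ANOVA are not tied to the waiting period; and the Discussion's 24-week evaluation has no untreated comparator.

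Conditional on choices the protocol leaves open: if all scheduled VAS times are used and the group main effect is tested, power falls from 90% to about 11-16% (five visits, full catch-up), 46-69% (five visits, half catch-up) or 36-65% (weekly VAS, full catch-up). A group-by-time test has 81-99.5% over five visits under full catch-up but does not isolate Tai Chi versus waiting. All these figures assume 48 per arm, d = 0.67 at week 8, compound symmetry with correlation 0.3-0.7 and the stated response profiles; the protocol gives neither an SD nor a correlation.

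**What to change.** - State that the primary comparison for both PSQI and VAS is the between-group difference at week 8, before controls start Tai Chi, adjusted for baseline.
- If a repeated-measures model is kept for VAS, report the week-8 contrast from it as the primary result, not a main effect averaged over visits.
- Label weeks 16, 32 and 40 as secondary comparisons of early with delayed start.
- For durability, align the arms by time since training (Tai Chi arm week 32 and control arm week 40, both 24 weeks after) and describe the result as uncontrolled. Amend the Discussion to match.

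Cost: wording in the protocol and analysis plan; no new visits or participants. The trial gives up any randomised claim against no treatment after week 8, which the design cannot support in any case.

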
Tai Chi, developed a few hundred years ago, is a traditional Chinese mind-body practice that combines physical, psychosocial, and social factors to promote health. It is an ancient discipline characterized by flowing circular movements of the upper limbs and constant weight shifting in the lower limbs (Peng, 2012; Dong et al., 2022; Song et al., 2022). Tai Chi has five forms: Chen, Yang, Wu, Sun, and Wu/Hao. Tai Chi is an exercise of mild-to-moderate intensity for older people (Siu et al., 2021a). Several studies have investigated the effects of Tai Chi on Parkinson's disease, diabetes, anxiety, depression, and so on Yeh et al. (2009); Li et al. (2012); Liu et al. (2020). Recent studies report Tai Chi to be a viable alternative for managing insomnia (Siu et al., 2021b). Tai Chi has been shown to have beneficial effects on insomnia in breast cancer survivors (Irwin et al., 2017). The study concluded that Tai Chi can effectively improve pain and disability in people with persistent low back pain (Hall et al., 2011; Liu et al., 2019). Tai Chi also has protective effects on the neuromuscular function of the lower extremities in aging patients with CNLBP (Zou et al., 2019). Tai Chi may be a potential alternative method to affect cognitive appraisal outcomes (Hall et al., 2016). However, it is unknown whether Tai Chi is an effective treatment for insomnia in patients with CNLBP.

We will conduct a randomized controlled trial to evaluate Tai Chi's effectiveness in managing insomnia in elderly people with CNLBP. We hypothesize that Tai Chi will be more effective in improving insomnia, pain, and physical and social functioning than the control group.

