### Participants

#### Sample size

This study will be designed to compare the effectiveness of the Tai Chi group against the control group. Sample size calculations will be based on the change in the Pittsburgh Sleep Quality Index (PSQI) and the Visual Analog Scale (VAS) scores. The study will detect a 5-point difference between groups on the PSQI scores (Irwin et al., 2008) and a 1.96-point difference in the VAS scores (Bower and Irwin, 2016). A total sample size of 96 participants will achieve 90% power with an alpha of 0.05. However, considering a 10% drop rate, we plan to recruit 106 patients.

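### The only nonparametric test named for scores is the Wilcoxon signed-rank test, which cannot compare two independently randomised arms

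*Protocol article*

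**What the plan says.** The Statistical analysis section of the protocol article names four methods:

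- A general method for two groups: "Two independent sample t-tests will be used for analysis".
- A method for VAS only: "Repeated measures analysis of variance will be used to examine the effects of VAS between the Tai Chi group and the control group".
- A method for data that are not normal: "We will use the Wilcoxon-Signed Rank Test to assess non-normally distributed data".
- A method for categories: "The chi-square test will be used for categorical data".

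Neither a rank-sum nor a Mann-Whitney test is mentioned anywhere in the article.

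The design and aim are stated elsewhere. Under Randomization and blinding: "Eligible participants will be randomly assigned to two groups in a 1:1 ratio". Under Sample size: "This study will be designed to compare the effectiveness of the Tai Chi group against the control group". The Introduction gives the hypothesis: "We hypothesize that Tai Chi will be more effective in improving insomnia, pain, and physical and social functioning than the control group".

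**The concern.** The signed-rank test works on differences within pairs, or on one sample against a fixed value. It needs a natural link between the two values in each pair, such as the same person before and after. A Tai Chi participant and a control participant have no such link here.

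If the sentence is followed literally for an outcome judged not normal, the analyst has two options. One is a before-after test inside each arm. The other is to pair unrelated people across arms. The first drops the randomised contrast, so natural improvement and regression to the mean count as change in both arms. It also invites the conclusion that Tai Chi works because its arm reached significance and the control arm did not. The second gives a result that depends on an arbitrary choice.

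PSQI is the more exposed of the two primary outcomes, because the only between-group method that covers it is the general t-test. That is the method a non-normality rule would displace.

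**Working it through.** **No stated figure to reproduce.** The point concerns the choice of test. The planned total of 96 is 48 per arm and the 106 recruited are 53 per arm; these serve only as simulation sizes below.

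**Step 1: test against design.**

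| Item | Protocol article | Implication |
|---|---|---|
| Allocation | 1:1 to two groups, in stratified blocks of varying size (Randomization and blinding) | Stratified blocks do not create matched pairs |
| Aim | Tai Chi against control (Introduction; Sample size) | A between-group test is needed |
| Parametric method | Independent two-sample t-test | The arms are treated as independent |
| Non-normal data | Signed-rank test | Paired or one-sample; does not match the rows above |

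The nonparametric counterpart of the independent t-test is the rank-sum test. No before-after objective is stated that would call for a paired test.

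**Step 2: forcing the test across arms.** With 48 and 46 observations it cannot be computed. With 48 in each arm, one simulated skewed data set was paired at random 2,000 times. The signed-rank p-value ran from 0.03 to 0.51 (median 0.23). The rank-sum test on the same data gave one answer, p = 0.038.

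**Step 3: using the test within arms (illustrative).** Assumptions: 53 per arm, no treatment effect, the same mean improvement in both arms, changes drawn from a normal distribution with SD 1, 4,000 trials per row. The improvement sizes are assumed; the protocol gives none.

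| Equal improvement in both arms | Tai Chi arm p < 0.05 (signed-rank) | Tai Chi p < 0.05 and control not | Rank-sum between arms p < 0.05 |
|---|---|---|---|
| 0.2 SD | 28.9% | 20.8% | 5.6% |
| 0.3 SD | 55.7% | 23.6% | 4.8% |
| 0.4 SD | 80.6% | 16.4% | 4.7% |

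The third column can be checked by hand. The arms are independent with the same rejection probability p, so the pattern has probability p(1 − p):

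- 0.289 × 0.711 = 0.205
- 0.557 × 0.443 = 0.247
- 0.806 × 0.194 = 0.156

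These agree with the simulation to within about 1 percentage point.

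The second column is the power of a within-arm test to detect an improvement that is real in the simulation. It is not a false-positive rate and should not be set against 5%. The third column becomes an error rate only if that pattern is used to claim efficacy.

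**Step 4: the same idea with skewed data.** Changes were drawn from a shifted gamma distribution with shape 2, 48 per arm, equal improvement of 0.5 SD, 4,000 trials. Within-arm signed-rank tests rejected in 84% (Tai Chi) and 85% (control). Exactly one arm, either one, was significant in 27%. Between arms, the rank-sum test rejected in 4.8% and the t-test in 4.6%.

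**The case against.** The strongest case on the other side has four parts.

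**The plan does name valid between-group methods.** A reader might infer that skewed outcomes are left with no valid between-group comparison at all. The text does not go that far. The t-test sentence carries no condition, VAS has its own between-group ANOVA, and nothing says in terms that the signed-rank test replaces either. This stands, and it narrows the point: the one nonparametric test named for scores cannot compare the arms. Replacement is the natural reading of a sentence that assigns a test to non-normal data, but it is a reading. The t-test also held its level in step 4, so a sound analysis is within reach.

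**Nothing shows that the rule will be triggered.** A reader might infer from the bounded scales (PSQI 0–21, VAS 0–10, ODI 0–100) and the pain-diary counts that it probably will be, even for a primary outcome. The article gives no distribution, SD or baseline data and no criterion for normality. A bounded scale is not evidence of skew, least of all for change scores. The inclusion criteria set no minimum PSQI or VAS, so scores near the floor are possible, but possible is as far as the document goes. This objection stands.

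**The protocol never says that within-arm results will decide efficacy.** Correct. The 16% to 24% range therefore describes a misuse that the wording permits, not the error rate of a stated rule. Step 3 also uses normal data; step 4 shows the same behaviour under skew.

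**It may be a slip between two similarly named Wilcoxon tests.** Quite possibly, but the text does not say so. The article announces a statistical plan still to be written, and a plan that copies the sentence would carry the error forward. This is a method wrongly named, not a detail left to a later document. The likelihood of a slip lowers the severity but does not remove the point.

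**Conclusion.** The concern holds in a limited form. The signed-rank test does not fit two independently randomised arms, the stated between-group aim, or the independent t-test named beside it, and it is the only nonparametric test named for continuous or ordinal scores. If it displaces the t-test for a non-normal outcome such as PSQI, the randomised comparison is lost for that outcome. VAS is less exposed because of its ANOVA.

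The size is conditional on three things: that the outcome is judged not normal, that the sentence is followed literally, and that within-arm results are read as evidence of efficacy. Under all three, with an assumed equal improvement of 0.2 to 0.4 SD and no treatment effect, a misleading pattern in favour of Tai Chi would appear in about 16% to 24% of trials, against about 5% for the rank-sum test.

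The rating is should-fix: it can be corrected before analysis, and design, data collection and sample size are untouched.

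**What to change.** Replace the signed-rank sentence in the Statistical analysis section, and carry the change into the statistical plan, with:

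*Between-group comparisons of non-normally distributed outcomes will use the Wilcoxon rank-sum (Mann-Whitney U) test. Any Wilcoxon signed-rank test will describe change within an arm only and will not be used to infer a treatment effect.*

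Naming one test is enough; offering a second rank-based method as an alternative would leave an open choice for the same outcome. The cost is one short replacement in the text, with no change to recruitment, visits, data or sample size.
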